### 8.3.2 Analysis of secondary endpoints

The number of severe exacerbations, the number of hospitalizations as well as the number of asthma-related events defined by use of antibiotics will be assessed by negative binomial regression with time within study as offset variable. Exacerbation-free survival time will be analyzed by Cox regression. Further secondary endpoints will be assessed by chi-square or Fisher's exact test for categorical variables or t-test or Mann-Whitney-U-test for continuous variables.

All tests are two-sided, and a p-value of less than 0.05 is considered to indicate statistical significance. Treatment differences will be displayed by hazard ratios, odds ratios, and 95% confidence intervals. All the analyses will be performed with the use of SAS® software, version 9.4 (SAS Institute).

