### 8.1 Sample size

Sample size calculations were based on results published by Vrijlandt E et al. (33). In this study, children aged 1–5 were treated with Tiotropium 5 µg vs placebo as add-on to ICS. After 105 days, 29% of the Tiotropium 5µg group had an asthma exacerbation with pneumonia or asthma worsening, whereas 55.9% of the placebo group had an event. For the present study, it can be assumed that most patients treated with ICS + placebo will suffer from one severe exacerbation within one year, therefore a rate of 90% of placebo patients with a severe exacerbation after one year is anticipated. For the Tiotropium group, a rate of 75% is assumed. The estimation of the difference in rates between the placebo and the Tiotropium group is performed conservatively, assuming a smaller difference than observed after 105 days in the study of Vrijlandt E et al (33). The assumed dropout rate of 15% is converted into a group-loss hazard (0.16) and considered in the sample size calculation. With an event rate of 90% in the control group and 75% in the Tiotropium group and a drop-out-rate of 15%, the sample size will amount to 152 patients when applying a two-sided log-rank test with a hazard ratio of 0.60, a significance level of  $\alpha = 0.05$  and a power of 0.8. The power calculation was performed with PROC POWER in SAS® 9.4.

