## Determination of primary and secondary measures

**The primary efficacy endpoint** is the time to first severe exacerbations defined by hospitalization and/or at least 3 days of systemic steroids or one day of rectal prednisolone (Rectodelt®). Severe exacerbations were chosen as primary outcome because they are patient-important outcomes that have significant consequences for children, caregivers, and the health care system.

**Key secondary endpoint(s) for all patients:** Secondary endpoints for all patients:

- Number of severe exacerbations
- Exacerbation-free survival time defined as the time from randomization until the first severe exacerbation.
- Percentage of patients requiring systemic corticosteroid rescue for asthma during the 52-week treatment period.
- Number of hospitalizations (severe exacerbation).
- Percentage of days and episodes of > 3 days with use of PRN salbutamol rescue medication during 52-week treatment period (non-severe exacerbation).
- Percentage of days without asthma symptoms assessed by TIPP diary App (PACD).
  - A day without asthma symptoms is defined as a day during which the patient experienced no asthma symptoms (daytime and overnight; question 1, 2, 5, 6, did not use rescue medication (salbutamol) (question 3 and 7), and had no asthma exacerbation/worsening requiring systemic corticosteroids, an unscheduled visit to a doctor's office, or hospital (question 11).
- Percentage of night-time awakenings due to asthma symptoms as assessed by the TIPP diary App.
- Health utilization defined as number of physician visits during treatment.
- Number of missed days in daycare.
- Number of asthma-related events defined by use of antibiotics.
- Evaluation of TRACK at V1, at V4 and at end of treatment.
- CGI-C at end of treatment.

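### The 52-week steroid-rescue percentage is left to chi-square or Fisher's test, which cannot use unequal follow-up, and two event counts default to tests with the same weakness

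*Protocol*

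**What the plan says.** Section 8.3 of the protocol lists among the secondary endpoints "Percentage of patients requiring systemic corticosteroid rescue for asthma during the 52-week treatment period". Section 8.3.2 names three counts for negative binomial regression "with time within study as offset variable": severe exacerbations, hospitalizations, and asthma-related events defined by antibiotic use. It names exacerbation-free survival for Cox regression. The remainder falls under one sentence: "Further secondary endpoints will be assessed by chi-square" or Fisher's exact test where the variable is categorical, with a t-test or Mann-Whitney test for continuous variables. Each test is read at the 5% level: "All tests are two-sided, and a p-value of less than 0.05 is considered to indicate statistical significance".

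The steroid percentage is not named, so as a categorical variable it goes to chi-square or Fisher. Two further endpoints, "Health utilization defined as number of physician visits during treatment" and the number of missed daycare days, are not named either.

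Three other places bear on this. Section 8.2 makes all randomized children the primary analysis population. Section 8.1 assumes 15% dropout. Section 8.3.1 has a dropout rule for the primary endpoint only: leaving for lack of efficacy is an event, and other leavers are censored. The Synopsis says that counts of events will be analysed by negative binomial regression and does not limit this to three of them.

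**The concern.** A percentage over 52 weeks is well defined only for children observed for 52 weeks or until they need steroids. With dropout planned, some children have neither. A chi-square test must count them as non-users, exclude them or impute them; it cannot censor them. The protocol deals with this for the primary endpoint and, through the offset, for three counts, but not for this endpoint. A child withdrawn for lack of efficacy without steroids could be a failure in the primary analysis and a success here.

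Two things are at stake. Dropout that differs between arms can create a difference where there is none. And if most children need steroids at some time in the year, a yes/no comparison discards the timing that carries much of the information.

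Raw totals of physician visits or missed days have the same weakness: less follow-up produces fewer of them.

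**Working it through.** **Inputs.** From section 8.1: one-year event rates of 90% and 75%, hazard ratio 0.60, loss hazard 0.16 per year, 152 children, two-sided 5% level, 80% power. These are rates for severe exacerbation; the protocol gives none for steroid rescue. Assumptions: 76 per arm (the ratio is not stated), exponential event times, dropout independent of the event.

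**1. The plan's own figure.** Events needed: 4 × (1.96 + 0.8416)² / (ln 0.60)² = 120.3, so 121. The chance of an observed event with event hazard λ and loss hazard γ over one year is λ/(λ+γ) × (1 − exp(−(λ+γ))). With λ = 2.303 (control), 0.6 × 2.303 (tiotropium) and γ = 0.16, this is 0.855 and 0.704, mean 0.780. Then 121/0.780 = 155.2, so 156 children, within 3% of the stated 152. Log-rank power at 152 is 0.794.

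**2. Same children, chi-square, leavers counted as event-free.** At 90% v 75% the observed proportions are about 85.5% and 70.5%. The standard error is 0.0672 under the null and 0.0661 under the alternative. Power = Φ((0.150 − 1.96 × 0.0672)/0.0661) ≈ 0.61. In simulation (20,000 trials) chi-square power was 0.61–0.62 and log-rank power 0.79; other runs put log-rank at 0.78. The gap is 17–18 points.

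**3. Where the gap comes from.** With no dropout at all, log-rank power is 0.81–0.82 and chi-square power 0.69 by formula (0.71 simulated), so 11–13 points remain. Dropout adds roughly 5–7. Only about 11 of 152 children leave before an event under these inputs. Excluding them instead gives chi-square power of 0.65.

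**4. Range over the unknown steroid-rescue rate** (hazard ratio 0.60, loss hazard 0.16, leavers counted as event-free):

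| Control rate | Tiotropium rate | Log-rank | Chi-square | Gap (points) |
|---|---|---|---|---|
| 90% | 74.9% | 0.794 | 0.614 | 18 |
| 80% | 61.9% | 0.730 | 0.631 | 10 |
| 70% | 51.4% | 0.661 | 0.598 | 6 |
| 60% | 42.3% | 0.585 | 0.543 | 4 |
| 50% | 34.0% | 0.504 | 0.474 | 3 |
| 40% | 26.4% | 0.417 | 0.396 | 2 |

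**5. Bias with no true effect.** Assume a 90% event rate in both arms, leavers counted as steroid-free, and unequal dropout (assumed; the protocol has a single 15%). Loss hazard = −ln(1 − dropout).
- 10% v 22% (0.105 v 0.248): 87.0% v 83.2%, a spurious 3.8 points. Chi-square type I error is about 0.10; log-rank stays at 0.05.
- 5% v 26% (0.051 v 0.301): 88.5% v 81.9%, a spurious 6.6 points. Chi-square type I error is about 0.21.

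In the first scenario, excluding the leavers keeps chi-square at about 0.05, so the distortion belongs to the steroid-free classification. Exclusion, however, departs from analysing all randomized children.

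**6. The two counts.** Mean follow-up in years is dropout/(loss hazard). For 10% v 22% this is 0.949 v 0.885, a ratio of 0.93; for 5% v 26% it is 0.975 v 0.864, a ratio of 0.89. At a constant event rate the raw mean count is therefore about 7% or 11% lower in the arm with more dropout, with no treatment effect.

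**The case against.** The strongest answer is that section 8.3.2 names tests, not a missing-data rule, and that section 8 leaves details to a SAP that is not at hand. A reader might infer that the protocol counts early leavers as steroid-free. It does not say so. That is the natural reading of a percentage of all randomized children, but the rule is open and the SAP may set it. Section 3.6.4 also asks that children withdrawing at their own request be followed up where possible. What stands is that the protocol itself chose the tests, and neither can censor.

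A reader might also infer that the endpoint loses nearly 20 points of power, and loses them through early leavers. Neither is supported. The 17–18 points borrow the severe-exacerbation rates, which is plausible because qualifying steroid courses are part of that event, but it remains an assumption. Most of the gap persists without dropout. Comparing proportions is a choice of what to estimate, no power is claimed for this endpoint, and a Cox analysis of a closely overlapping event is already primary.

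The unequal dropout figures are hypothetical and show direction and scale only.

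On the counts, it is fair to reply that the Synopsis points to negative binomial regression and that section 8.3.2 never expressly sends visits or missed days to a t-test. They arrive there by default, so the two places need aligning. A missing log in the offset wording is shorthand and not a point of substance.

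**Conclusion.** The concern holds in a limited form. Chi-square or Fisher on a 52-week percentage in all randomized children cannot account for early leavers, and the protocol does not say how they are classified. If they count as steroid-free and dropout is unequal, the arm with more dropout is favoured: about 4 points at 10% v 22% and 6.6 at 5% v 26%, with a 90% event rate and no true effect. The power cost is conditional: about 61% against 78–79% at the borrowed 90% v 75%, falling to 10 points at an 80% control rate and 2 at 40% with a hazard ratio of 0.60. It comes mainly from discarding timing. All figures assume 76 per arm, exponential times and dropout independent of the event.

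Physician visits and missed daycare days fall by default to tests that ignore follow-up, out of line with the Synopsis. None of this touches the primary analysis. It should be corrected because it affects what will be reported as significant at 5%.

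**What to change.** In section 8.3.2:
- Compare time to first systemic steroid course for asthma with the primary endpoint's Cox model and its dropout and censoring rule. Report Kaplan-Meier 52-week percentages by arm in place of raw percentages.
- Analyse physician visits and missed daycare days by negative binomial regression with a follow-up-time offset, in line with the Synopsis.

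This takes a few sentences. Section 5 already has all medication recorded on the concomitant therapy eCRF throughout the trial, and all the methods are already in the plan. The small downside is that the endpoint is then expressed as a hazard ratio with Kaplan-Meier percentages and overlaps with the primary analysis.

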| SECONDARY ENDPOINTS  | 
Key secondary endpoint(s): number of severe exacerbations, number of hospitalizations (severe exacerbation), (severe) exacerbation-free survival time, number of asthma-related events defined by use of antibiotics, percentage of night-time awakenings due to asthma symptoms as assessed by the electronic patients diary/PACD, percentage of days without asthma symptoms assessed by TIPP diary App (PACD), , percentage of days and episodes of > 3 days with use of PRN salbutamol rescue medication, health utilization (number of physician visits), number of missed days in daycare, result of TRACK, CGI-C at end of treatment and potential biomarkers for treatment response:
 
Eosinophils, IgE, specific IgE to common allergens (birch, grass, Dermatophagoides pteronyssinus, Alternaria, Cladosporium, cat, dog, hen's egg, cow's milk and peanut.
 
Assessment of safety:
Safety will be ensured by analysis of symptom scores and rescue medication use by the electronic diary, and adverse events (AEs).
                                                                                                                                                  |
| STATISTICAL ANALYSIS | 
Efficacy:
The comparison between groups will be made by time to first severe exacerbation within 12 months of therapy.
 
Description of the primary efficacy analysis and population:
The time to first severe exacerbation will be analyzed by Cox regression with factor treatment and the covariates age group and center. Analyses will be performed in the intention-to-treat population and repeated in the per-protocol population as sensitivity analyses. Treatment differences will be displayed by hazard ratios and 95% confidence intervals.
 
Safety: For safety analyses, frequencies of patients experiencing at least one adverse event (AE) will be displayed by system organ class and preferred term according to MedDRA terminology.
 
Secondary endpoints:
For secondary analyses, Cox regression for time to event data will be used and negative binomial regression for count of events. Further secondary endpoints will be assessed by chi-square or Fisher's exact test for categorical variables or t-test or Mann-Whitney-U-test for continuous variables.
 
All tests will be conducted on a two-sided significance level of alpha = 0.05.
 |

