### **2.2 Secondary objectives**

The secondary objective is to evaluate whether addition of Tiotropium via Respimat® to ICS reduces health utilization (hospitalizations, physician visits, antibiotic use) in partial or uncontrolled preschool asthma.

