## 8 STATISTICS

Details of the statistical analysis of the data collected in this trial will be documented in a Statistical analysis plan (SAP) that will be generated by IZKS Mainz and finalized before closing the database and prior to breaking the blind. The SAP is based on the protocol including all amendments. The document may modify the plans outlined in this protocol; however, any major modifications of the primary endpoint definition and/or its analysis will also be reflected in a protocol amendment. Any deviation from the original statistical plan must be described and justified in the final report. The statistical analysis will be conducted using SAS®.

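### Section 8.3.2 and the synopsis let every secondary test be called significant at p < 0.05, with no order, gate on the primary, alpha allocation or exploratory label for about a dozen endpoints

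*Protocol*

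**What the plan says.** The primary analysis (section 8.3.1) is one Cox comparison of time to first severe exacerbation in the ITT population, at a two-sided 5% level. Section 8.3.4 plans no interim analysis.

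For the secondary endpoints, section 8.3.2 states: "All tests are two-sided, and a p-value of less than 0.05 is considered to indicate statistical significance". The synopsis says: "All tests will be conducted on a two-sided significance level of alpha = 0.05".

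The list in section 8.3, repeated in section 6.1, has 12 bullets headed "Key secondary endpoint(s) for all patients". The synopsis uses the key secondary label for a similar list. Section 3.4 gives the 12 bullets as secondary endpoints without the word key. One bullet is the primary endpoint under another name: "Exacerbation-free survival time defined as the time from randomization until the first severe exacerbation".

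The secondary objective in section 2.2 is to evaluate whether adding tiotropium "reduces health utilization (hospitalizations, physician visits, antibiotic use) in partial or uncontrolled preschool asthma".

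No section puts the secondary endpoints in order, divides alpha among them, ties them to the primary result or labels them exploratory. Section 8 says of the SAP: "The document may modify the plans outlined in this protocol".

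**The concern.** Section 8.3.2 states a decision rule, so this is more than a detail left for later. Where the protocol means to defer to the SAP it says so: subgroups (8.3.3), and additional covariates and the per-protocol effect (8.3.1). It does not defer the criterion for secondary significance.

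A report that follows this rule may call tiotropium significantly better on any endpoint that reaches p < 0.05, including when the primary comparison fails. With about a dozen endpoints at the full 5% each, such a result can easily arise by chance. The secondary objective is most exposed: it names three components, each would be tested at 5%, and nothing says how many must succeed.

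**Working it through.** **The plan's own figure.** The protocol gives no familywise error for the secondary endpoints, so there is none to reproduce.

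**Inputs from the protocol.**
- Level per test: two-sided 0.05, critical value 1.96 (section 8.3.2, synopsis).
- Bullets in the section 8.3 list: 12.
- Minus 1 for exacerbation-free survival time, which repeats the primary: 11.
- Plus 1 because one bullet holds two measures, days and episodes: "Percentage of days and episodes of > 3 days with use of PRN salbutamol rescue medication during 52-week treatment period".
- Plus 1 because TRACK has two post-baseline time points, V1 being baseline: "Evaluation of TRACK at V1, at V4 and at end of treatment".
- Tests counted: 12 − 1 + 1 + 1 = 13. They are: number of severe exacerbations, systemic steroid rescue, hospitalizations, salbutamol days, salbutamol episodes, symptom-free days, night-time awakenings, physician visits, missed daycare days, antibiotic-defined events, TRACK at V4, TRACK at end of treatment, and CGI-C.
- Components of the section 2.2 objective: 3.

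**Assumptions, not in the protocol.** All secondary null hypotheses are true. The test statistics are normal with a common correlation ρ, shown at 0, 0.5 and 0.8.

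**Formulas.** For ρ = 0, the chance of at least one p < 0.05 among k tests is 1 − 0.95^k. In tiotropium's favour only, it is 1 − 0.975^k.
- k = 13: 1 − 0.95^13 = 1 − 0.513 = 48.7%; in favour, 1 − 0.975^13 = 1 − 0.720 = 28.0%.
- k = 3: 1 − 0.95^3 = 1 − 0.857 = 14.3%; in favour, 1 − 0.975^3 = 1 − 0.927 = 7.3%.

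For ρ > 0, each statistic is √ρ·W + √(1−ρ)·e, with W shared by all tests. The chance of at least one significant result is 1 − ∫ φ(w)·[Φ((1.96 − √ρ·w)/√(1−ρ)) − Φ((−1.96 − √ρ·w)/√(1−ρ))]^k dw, integrated numerically. Dropping the second Φ term gives the favourable direction.

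| Tests | Direction | ρ = 0 | ρ = 0.5 | ρ = 0.8 |
|---|---|---|---|---|
| 13 | either | 48.7% | 33.4% | 19.2% |
| 13 | favours tiotropium | 28.0% | 16.7% | 9.6% |
| 3 | either | 14.3% | 12.5% | 9.8% |
| 3 | favours tiotropium | 7.3% | 6.3% | 4.9% |

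A single test has 5% in either direction and 2.5% in favour.

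**Sensitivity to the count.** With the 11 distinct bullets as one test each, the either-direction figures are 43.1%, 30.4% and 18.0%. The conclusion does not depend on splitting the salbutamol and TRACK bullets.

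**The case against.** The strongest reply is that secondary multiplicity is commonly handled in a SAP. Section 8 allows the SAP to modify the protocol's plans and requires an amendment only for major changes to the primary endpoint or its analysis. The SAP is not shown, so lack of control is known only for the protocol. That stands as a limit. It does not remove the point, because the protocol already states a rule, and a SAP that followed it would carry it forward.

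The confirmatory error rate is also intact: one primary hypothesis, no interim analysis, and no passage letting a secondary result rescue a failed primary. This too stands, and it keeps the point small.

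The key secondary label is weak evidence of a confirmatory tier. The headings in 6.1 and 8.3 run the key and plain labels together, and section 3.4 uses only the plain one. The point therefore rests on the significance rule, not the label.

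A reader might infer stronger versions that the protocol does not support:
- *A single figure of one in three, or one in eight for the objective.* Both need a correlation of 0.5, which the protocol does not give, and both count errors in either direction, although the claim to guard against is benefit.
- *That one positive component meets the secondary objective.* Section 2.2 says only that the effect will be evaluated. The 10% to 14% applies only if a report took any one component as success.
- *That the lung-function tests should be added to the count.* They sit under a separate heading and apply to a subset of children aged 4 and older, and the 30-minute comparison is worded as post-dose against pre-dose, not between groups.

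**Conclusion.** The point holds as a limited and cheap improvement. The protocol declares every secondary test significant at two-sided p < 0.05 without any form of error control. If no secondary endpoint truly differs, the chance of at least one such declaration among 13 all-patient tests is about 19% to 49%, of which about 10% to 28% is the chance of at least one in tiotropium's favour. For the three components of the objective it is about 10% to 14%, or 5% to 7% in favour, conditional on any one being read as success. These ranges rest on the global null, a common correlation between 0.8 and 0, and the count shown above. The primary test, its type I error and the sample size are unaffected, and the documents do not show whether the SAP already adds control.

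**What to change.** In section 8.3.2 and the synopsis, limit the statement of statistical significance to the primary test. State that all secondary, lung-function and subgroup results are exploratory, reported as estimate, 95% confidence interval and nominal p-value.

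If the sponsor wants confirmatory secondary claims, it should pre-specify before unblinding a short sequence of its own choosing. The sequence is tested only if the primary is significant, each step at two-sided 5%, stopping at the first non-significant result. The key secondary label in the synopsis, 6.1 and 8.3 should then cover only those endpoints. The choice and order are the sponsor's; the protocol does not say that the order of words in section 2.2 is a priority order.

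The SAP should carry the same text. The change needs no new data, visits or patients. Its cost is that fewer secondary results can be called significant, and none if the primary fails.
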